## Statistical methods

Baseline characteristics of patients (eg, gender, age, allergies and comorbidities), use of antimicrobial drugs, appropriate antimicrobial therapy and other outcome parameters will be described by entity.

To mitigate possible differences in time trends and baseline characteristics at patient and centre level, primary analysis will be by centre and effect estimates will be combined over centres using meta-analytic methods. These primary analyses will employ multivariable multilevel logistic models with time periods as fixed effects to adjust for time trend and treatment as fixed effect to estimate the OR of treatment. Entities (ward/specialty) will be included as a random effect to account for the correlation of patients within entities, assuming this correlation is independent of time period of including the patient. Moreover, covariates will be included to adjust for age, gender, hospital and specialty (medical, surgical). Similar models but using (generalised) linear multilevel models will be used for continuous outcomes or incidence/rate outcomes.

Sensitivity analyses may include the following: adjusting for additional confounders if imbalance at baseline is present; investigating deviations from the assumption that the correlation of patients within entities is independent of time period of including the patient; estimating differences in percentage (instead of odds ratios) using a (generalised) linear multilevel models with identity link and binomial error distribution and incorporating the three centres in one model.

Subgroup analysis for specialty and other factors as appropriate will be conducted.

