### Sample size

By including 24 entities (wards/specialties) with seven measurement periods (including one baseline period) in which the primary outcome (appropriate empiric antimicrobial drug use) will be measured in 15 participating patients per entity per time period and an assumed intra-entity correlation coefficient of 0.1, the study has a power of 81% to detect an absolute improvement in appropriate antimicrobial use by 10 percentage points from of 60% to 70%.^16^ To account for potential drop-outs or a lower inclusion rate, we aim to include 36 clusters in the three participating hospitals.

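### The primary model assumes that within-entity correlation does not depend on period, so its confidence interval is too narrow if entities drift separately; relaxing this is only an optional sensitivity analysis

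*Protocol article*

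**What the plan says.** All of this is in the protocol article.

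- **Random part of the primary model** (Statistical methods): "Entities (ward/specialty) will be included as a random effect to account for the correlation of patients within entities". There is no entity-by-period term. The section attaches a condition to this random effect, namely "assuming this correlation is independent of time period of including the patient".
- **Fixed part** (same section): "time periods as fixed effects to adjust for time trend and treatment as fixed effect to estimate the OR of treatment".
- **Combination over hospitals** (same section): "primary analysis will be by centre and effect estimates will be combined over centres using meta-analytic methods". Common-effect or random-effects pooling is not specified.
- **The check on the assumption** (same section): the list opens with "Sensitivity analyses may include the following" and contains "investigating deviations from the assumption that the correlation of patients within entities is independent of time period of including the patient". No alternative model is named.
- **Sample size**: "an assumed intra-entity correlation coefficient of 0.1", one value, with no separate between-period correlation.

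**The concern.** A stepped-wedge estimate relies heavily on changes within an entity from one period to the next. The planned model treats two patients in the same entity and month as no more alike than two patients of that entity six months apart. If each entity has its own ups and downs by period, that scatter enters the treatment estimate but not its standard error. A binomial model has no free residual variance to absorb it.

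The article itself gives reasons to expect some drift. Its list of strengths and limitations says physicians move between wards or specialties. The Intervention section provides for withdrawing app access when they do. The justification of the design says prescribing decisions are made by teams.

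What is at stake is the primary interval and p-value: too narrow an interval makes a false claim that the app works more likely.

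**Working it through.** **Inputs from the article.** 6 introduction moments, 7 periods, 15 patients per entity and period, ICC 0.1, 60% versus 70%. There are 24 entities in the power calculation and 36 planned, two per hospital per step, so 2 × 6 = 12 per centre.

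**Assumptions.** Two-sided 5% level (none is stated). Total variance 0.225, the mean of 0.6 × 0.4 = 0.24 and 0.7 × 0.3 = 0.21. CAC from 0.5 to 1 (no value is given).

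**The plan's own figure.** The standard stepped-wedge calculation with 24 entities and no drift gives power of 89.9%. It gives 87.9% to 91.7% for total variances of 0.24 to 0.21, and 84.4% to 88.8% if those are taken as residual variances. The stated 81% is not reproduced from the stated inputs alone. It is lower than the standard result, and this point does not depend on it.

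**Step 1, variance components.**
- Entity variance under the plan: 0.1 × 0.225 = 0.0225.
- Sampling variance of an entity-period mean: 0.2025 / 15 = 0.0135.
- With drift, the entity-by-period variance is 0.0225 × (1 − CAC). At CAC 0.8 this is 0.0045, one third of 0.0135, and the planned model ignores it.

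**Step 2, reported and true standard error.** With V_m the planned covariance, W its inverse and V the true covariance:
- reported variance = [(X′WX)⁻¹] for treatment;
- true variance = [(X′WX)⁻¹ X′WVWX (X′WX)⁻¹] for treatment;
- type I error = 2Φ(−1.96 × SE reported / SE true).

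With 36 entities and V_m at ICC 0.1, the reported SE is 2.52 percentage points.

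| CAC | True SE (points) | SE ratio | Type I error |
|---|---|---|---|
| 1 | 2.52 | 1.000 | 5.0% |
| 0.95 | 2.62 | 0.964 | 5.9% |
| 0.9 | 2.71 | 0.931 | 6.8% |
| 0.8 | 2.88 | 0.875 | 8.6% |
| 0.5 | 3.35 | 0.753 | 14.0% |

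If the planned model re-estimates its ICC under drift, the last two become 8.4% and 13.0%. If correlation instead decays by a factor of 0.9 or 0.8 per period, type I error is 10.0% or 13.9%.

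**Step 3, the planned analysis simulated.** Setting: no app effect, 3 centres × 12 entities, 15 per cell, ICC about 0.1, one random-intercept logistic model per centre. The ranges cover separate simulations of 2,500 to 6,000 trials per scenario. Monte Carlo error is about 0.4 to 0.6 points near 8-9%, for example √(0.087 × 0.913 / 2,500) = 0.56 points.

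| CAC | Common-effect pooling | Random-effects (DerSimonian-Laird) pooling |
|---|---|---|
| 1 | 4.7-6.8% | 4.9% |
| 0.9 | 6.1-7.4% | 4.6-5.0% |
| 0.8 | 8.3-8.8% | 5.3-5.9% |
| 0.5 | 11.1-12.1% | 6.9-7.3% |

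**Step 4, the remedy simulated.** With an entity-by-period random intercept added:
- Common-effect pooling: 8.4% falls to 7.1% and, in a second simulation, 8.8% to 7.2% (CAC 0.8); 12.1% falls to 7.4% (CAC 0.5).
- Random-effects pooling: 5.9% falls to 4.9% and 5.5% to 4.5% (CAC 0.8); 7.3% falls to 4.9% (CAC 0.5).
- The extra variance was estimated as about zero in 28% of centre fits at CAC 0.8 and 51% at CAC 0.9, which is part of why the recovery is incomplete.

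**Step 5, precision and power with the correct correlation.**

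| CAC | 95% CI half-width, 36 entities | Power, 36 entities | Power, 24 entities |
|---|---|---|---|
| 1 | 4.95 points | 97.7% | 89.9% |
| 0.9 | 5.30 | 95.9% | 85.5% |
| 0.8 | 5.62 | 93.7% | 81.2% |
| 0.5 | 6.35 | 87.0% | 71.2% |

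The widening is 5.30 / 4.95 = 1.07 at CAC 0.9 and 5.62 / 4.95 = 1.14 at CAC 0.8.

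**The case against.** **The assumption is disclosed and a check is listed.** That is so, and this is not an oversight. A full analysis plan may also name the alternative model. What stands against it is that the article fixes the simpler structure as primary. An optional check does not change the primary interval.

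**No drift value comes from the documents.** Also true. Period effects fitted separately by centre absorb any drift common to a centre's entities, so only entity-specific drift matters. The rollout lasts 2 + 6 × 4 = 26 weeks. At CAC 0.95 the error is small.

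**The size depends on pooling.** This stands. Under random-effects pooling, constant drift down to CAC 0.8 does little harm. Some protection is lost at CAC 0.5, and coverage is 91.7% if correlation decays by 0.8 per period. The article does not commit to that pooling.

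**Not all of the excess is drift.** With common-effect pooling, one simulation already gave 6.8% without drift, because each centre has only 12 entities; others gave 4.7% to 5.8%.

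**Power of 94% counts the reserve.** The Sample size section adds the extra 12 entities against drop-out and low inclusion. The 24-entity column is therefore the cautious one.

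A reader might infer from the 81.2% at CAC 0.8 with 24 entities that the sample size already allows for drift. The article says nothing of the kind, and other unstated assumptions also give about 81%.

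**Conclusion.** The point holds in conditional form. The article commits the primary analysis to a correlation structure that makes the interval too narrow whenever entities drift separately. The direction was the same in every drift scenario tried. At CAC 0.8, type I error is about 8-9% instead of 5% with common-effect pooling and about 5-6% with random-effects pooling. At CAC 0.95 or above the effect is minor.

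A reader might go further and conclude that the primary result will be anti-conservative, or that the trial cannot support a claim without this change. The documents do not support that. They give neither the between-period correlation nor the pooling method, and the assumption is stated openly with a check listed. This is an inexpensive improvement that should be made, not a fatal defect.

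**What to change.** In Statistical methods:

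1. Make the primary model in each centre one with random intercepts for entity and for entity-by-period. Keep the entity-only model as a sensitivity analysis that will be done.
2. In the same amendment, either state a small-sample correction or name the pooling method. The added term alone leaves about 7% under common-effect pooling.

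**Cost.** No new data and a few sentences of text. Without drift, simulated type I error was almost unchanged (5.6% against 5.4% with common-effect pooling). With drift, intervals are about 7% (CAC 0.9) to 14% (CAC 0.8) wider. Power at CAC 0.8 is about 94% with 36 entities and about 81% with 24; at CAC 0.5 with 24 it is about 71%. These power figures use a normal reference and one linear model. A t reference with 22 degrees of freedom lowers the 81% to 77.6%. The power cost of random-effects pooling over three centres was not calculated.

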### Sample size

By including 24 entities (wards/specialties) with seven measurement periods (including one baseline period) in which the primary outcome (appropriate empiric antimicrobial drug use) will be measured in 15 participating patients per entity per time period and an assumed intra-entity correlation coefficient of 0.1, the study has a power of 81% to detect an absolute improvement in appropriate antimicrobial use by 10 percentage points from of 60% to 70%.^16^ To account for potential drop-outs or a lower inclusion rate, we aim to include 36 clusters in the three participating hospitals.

## Ethics and dissemination

This protocol has been approved by the institutional review board (IRB) of each participating centre. Ethical approval has been obtained from the Medical Ethics Committee Erasmus MC, Rotterdam, the Netherlands, number MEC-2019–0172, the Swedish Ethical Review Authority, Uppsala, Sweden, number 2019-05075 and from the Commission cantonaled'éthique de la recherche, Geneva, Switzerland, number 2019-01061. Physicians will be informed about the app without obligation to use it, furthermore analysis of usage will be anonymous, therefore a waiver for informed consent for physicians has been asked. However, participating physicians will be asked for a digital informed consent the first time they use the app. To monitor patient data, consent will be asked according to the country legislation and IRB mandate.

### Dissemination

Results will be disseminated to healthcare professionals and researchers via presentations at national and international conferences and publications in peer-reviewed journals. Furthermore, we plan to have a workshop with interested healthcare workers after the end of the study to disseminate experiences and findings. The public will be informed through press releases.

General project data and metadata will be included in the supplementary data of published articles if needed, and/or shared through university repositories.

## Discussion and implications

To date, few IT-based AMS interventions have been evaluated in randomised clinical trials.^4 10 11^ Clinical decision making by means of clinical decision support systems (CDSS) integrated in the EHR present the ‘gold standard’ of IT-based AMS. However, their widespread use has been limited by some major obstacles: (1) EHRs are still not universally implemented in all hospitals in high-income countries, and even less so in low-income and middle-income countries (2) even if an EHR is implemented it usually lacks essential components for CDSS such as a computerised physician order entry system and (3) EHRs—especially those of commercial vendors—have designs that are difficult to modify/adapt. By developing an ‘app’ as a software programme running on smartphones and other mobile devices such as tablets, an intermediate or complementary step to full CDSS may be offered. Spectrum is a smartphone-based digital stewardship app that is customisable to local guidelines by local AMS teams. In our stepped-wedge cluster randomised trial we will evaluate the impact of this app on appropriate antimicrobial prescribing in high-income countries. However, smartphone adoption is consistently strong in middle-income countries such as in the Caribbean and reached low-income countries in Africa.^17 18^ More and more healthcare workers have their own electronic devices (smartphone or tablets).^7^ AMS smartphone-based interventions can be made easily available, in high-income, low-income and middle-income countries. The ability of this app will make antibiotic prescription guidelines more accessible for physicians all over the world, thereby helping to fight AMR.
